#### Concealment mechanism {16b}

Treatment allocation is managed as described above. The opaque boxes containing study medicine or placebo are identical besides the assigned unique allocation ID written on the box. Treatment assignment during the trial is only available for the including CCU physician and the accompanying medical assistant manning the CCU following screening of the patient and contact with the trial guardian for informed consent. Once informed consent is obtained, the including physician opens a random opaque box and infuse the content, i.e., study medicine or placebo. The box allocation number will be available at all time through information filled out in the pre-hospital journal, consent by the including physician and/or the delivery of the used box at the department of admission.

#### Implementation {16c}

Allocation of study medicine and placebo will be done by the pharmacy as described in {16a}. After inclusion and completion of study drug infusion, the including CCU physician will complete an electronic consent through REDCap with allocation number and confirm that inclusion is made following contact and consent from the trial guardian. No in-hospital personnel will have knowledge of allocation at any time and the including physician will not take further part in treatment of the patient. At trial completion the investigators will be informed of allocation.

### Blinding {17}

#### Who will be blinded {17a}

All in-hospital personnel, research personnel, and patients will be blinded to intervention allocation throughout the trial. The including pre-hospital CCU physician and the medical assistant will be blinded during screening, inclusion, and randomization of the patient, but unblinded upon breaking concealment of the randomized box. Infusion is completed before arrival at the hospital and no information other than allocation number will be given at hospital admission. When follow-up is completed, and data collected, the database will be locked and treatment allocation will be unblinded.

#### Procedure for unblinding {17b}

Information on treatment allocation is kept in concealed envelopes in a safe available to authorized personnel at each site. Unblinding will only occur if the knowledge is necessary for treatment of the patient or in case of safety reporting for the involved authorities. In any case of unblinding, the PI will be contacted beforehand. The unblinding will be documented in the trial master file and the patient’s electronic case report fil (eCRF), and the sponsor-investigator will be informed within 1 day.

## Methods: data collection, management, and analysis

### Data collection

#### Assessment of outcomes {18a}

Patient data will be handled as ordinary chart records. All data will be kept according to national legislation, i.e., the General Data Protection Regulation (GDPR) and the Data Protection Act. Acceptance of the data handling and management will be applied for at these institutions before initiation of the study. All handling of personal data in the study is the responsibility of the principal investigator. The study database will be constructed in accordance with national legislation and local practice. Data is entered by study personnel and the database will be maintained for 15 years and anonymized if requested by relevant authorities. Data will be monitored by the Good Clinical Practice (GCP) unit, including review of consent forms and eligibility for the trial. The frequency of onsite monitoring will depend on compliance with the protocol, number of enrolled patients, and the quality of data handling. The principal investigator will be responsible for all data in the eCRF. At completion of the study, biomarkers will be analyzed, and data will be stored in an encrypted server with a backup function.

#### Participant retention and follow-up plan {18b}

Patients included are expected to remain in the ICUs the first three days of admission until the primary endpoints are collected. If a patient awakes and is transferred to the ward, blood sampling will be done here, including samples for the research biobank to analyze the primary endpoints. If a patient is transferred to a local hospital within three days of admission, samples for the biobank are not taken but standard biochemistry will be taken routinely and will be collected. At both sites, dedicated staff will be responsible for follow-up in the ambulatory setting at approximately 90 days following OHCA. The patient will be offered a visit at home if an ambulatory visit is not possible or not wanted by the patient. Patients who discontinue the study during follow-up will remain in the study database if an informed consent is obtained. After 180 days patients will be evaluated through a telephone interview.

### Data management {19}

The database system REDCap® is used for data storage. REDCap is hosted and maintained by the Regional IT department, and data quality will be monitored as described in the “ Assessment of outcomes {18a}” section.

### Confidentiality {27}

Patient confidentiality will be ensured throughout the trial according to national and international legislation (GDPR and the Data Protection Act). Data entered in REDCap are encrypted and will only be assessed by dedicated personnel. After trial completion, the biobank material analyses will be stored in a secured server, and the results from the trial will only be available upon request if approval is provided by relevant authorities.

### Plans for collection, laboratory evaluation, and storage of biological specimens for genetic or molecular analysis in this trial/future use {33}

A research biobank is established from trial initiation and biological material is stored according to legislation and approvals. The material will be analyzed at an advanced laboratory following inclusion of the last participant. Currently, no genetic studies are planned, and future studies including the material are only possible with approval from relevant authorities.

### Statistical methods

#### Statistical methods for primary and secondary outcomes {20a}

Analyses of primary and secondary outcomes will be conducted on the intention-to-treat population. Categorical variables will be presented as numbers and continuous variables will be presented as mean (± SD) or median (25th percentile–75th percentile), according to distribution. The primary analyses of the co-primary endpoint will include the modified intention-to-treat population.

Further, we will conduct sensitivity analyses of the co-primary endpoint including all randomized patients. In this analysis, values missing because a patient died prior to blood sampling will be replaced with the median value of the given biomarker in patients dying after blood sampling, but before 30 days.

Continuous endpoints, including the co-primary endpoint, will be assessed at multiple time points and analyzed by application of linear mixed models of covariance. For approximation of normal distribution, logarithmic transformation will be done, as appropriate. The application of linear mixed models will ensure that a higher power is achieved compared to the sample size calculation, which is based on a single measurement (see the “Sample size {14}” section). For analyses of categorical secondary outcomes, chi-squared or Fisher’s exact test will be applied.

Cox proportional hazard models will be applied and sequentially adjusted for the interaction between treatment arm and relevant variables (sex, age, primary ECG rhythm, time to ROSC, pPCI performed, NSE-, and IL-6 levels). Differences in mortality between treatment arms will be depicted in Kaplan–Meier estimate plots and compared with the log-rank test.

R Studio, version 1.2.5001, will be used for all analyses (RStudio Team [2020]. RStudio: Integrated Development for R. RStudio, PBC, Boston, MA; URL: http://www.rstudio.com/).

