**Methods:**

The study is an investigator-initiated, randomized, multicenter, single-blinded, placebo-controlled, clinical trial. Inclusion will continue until one hundred twenty unconscious OHCA patients surviving a minimum of 72 h are randomized. Intervention is a 1:1 randomization to an infusion of methylprednisolone 250 mg following a minimum of 5 min of sustained return of spontaneous circulation in the pre-hospital setting. Methylprednisolone will be given as a bolus infusion of 1 × 250 mg (1 × 4 mL) over a period of 5 min. Patients allocated to placebo will receive 4 mL of isotonic saline (NaCl 0.9%). Main eligibility criteria are OHCA of presumed cardiac cause, age ≥ 18 years, Glasgow Coma Scale ≤ 8, and sustained ROSC for at least 5 min. Co-primary endpoint: Reduction of interleukin-6 and neuron-specific-enolase. Secondary endpoints: Markers of inflammation, brain, cardiac, kidney and liver damage, hemodynamic and hemostatic function, safety, neurological function at follow-up, and mortality. A research biobank is set up with blood samples taken daily during the first 72 h from hospitalization to evaluate primary and secondary endpoints.

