### Outcomes {12}

#### Primary outcome

The primary outcome is the repeated daily measurements of IL-6 and NSE at admission and the following 24, 48, and 72 h after admission.

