## Discussion

The aim of this study is to investigate whether an early infusion of 250 mg methylprednisolone can mitigate the systemic inflammatory response seen in comatose patients resuscitated after OHCA. The co-primary endpoints investigated are the biomarkers IL-6, and NSE and we expect to find a reduction of 20% for both biomarkers measured daily from admission to 72 h following admission.

Inflammation has a key role in the complex systemic response, PCAS. Previous findings have shown that circulating levels of inflammatory biomarkers such as IL-6 are associated to outcome following OHCA, i.e., neurological function and death [9, 31]. A possible clinical benefit of early anti-inflammatory treatment in OHCA remains unknown, but several studies targeting inflammation have promising results. Two small studies from 2009 and 2013 found improved survival and neurological outcome following a combination of epinephrine, vasopressin, and glucocorticoid in patients suffering from IHCA [24, 25]. In both of these studies, glucocorticoid intervention was a low dose of 40 mg methylprednisolone injected during CPR and subsequently patients who developed shock were treated with stress-dose hydrocortisone for a maximum of 7 days. Further, a similar recent Danish study in IHCA patients compared the combination of vasopressin and methylprednisolone (40 mg) with placebo administered during CPR and found the combination to be associated with a higher rate of ROSC, but not survival [26]. The most important difference from these studies compared to the present study was the timing (intra-arrest administration) and dosage (40 mg VS 250 mg) of glucocorticoid. The populations studied consisted of IHCA patients, which in a recent observational study has been found to be similar to OHCA patients in demographics, but with a higher burden of cardiovascular comorbidity [32]. Based on current evidence, ILCOR and the European Resuscitation Council do not support the use of glucocorticoids neither as intra-arrest- or post-cardiac arrest treatment in IHCA and OHCA [33, 34]. However, further evidence could clarify the optimal use and possible role of glucocorticoids in cardiac arrest treatment.

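### The Cox models condition the treatment effect on NSE and IL-6, which are co-primary endpoints first measured after the study drug, so those hazard ratios do not estimate the total effect on death

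*Protocol article*

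**What the plan says.** Under statistical methods {20a} the protocol article states: "Cox proportional hazard models will be applied and sequentially adjusted for the interaction between treatment arm and relevant variables". The interaction is spelled out as one between "treatment arm and relevant variables (sex, age, primary ECG rhythm, time to ROSC, pPCI performed, NSE-, and IL-6 levels". The sentence names no endpoint. The next one names mortality, which is to be shown in Kaplan-Meier plots and compared by the log-rank test.

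On timing, the blinding section {17a} says: "Infusion is completed before arrival at the hospital". The primary outcome section defines the outcome as "repeated daily measurements of IL-6 and NSE at admission and the following 24, 48, and 72 h after admission". No sample before the drug is described.

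On the role of the two markers, the abstract has "Co-primary endpoint: Reduction of interleukin-6 and neuron-specific-enolase", and the discussion adds: "we expect to find a reduction of 20% for both biomarkers measured daily from admission to 72 h following admission".

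**The concern.** A covariate in a treatment-effect model should be fixed before treatment starts. Of the seven variables listed, sex, age, primary ECG rhythm and time to ROSC meet that condition. pPCI, NSE and IL-6 do not.

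NSE and IL-6 matter most, because on the trial's own hypothesis they lie on the pathway from drug to outcome. Conditioning on them has three effects:

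- It removes whatever part of the drug's effect on death passes through them.
- It can introduce bias from unmeasured severity that raises both the marker and the risk of death.
- It makes an interaction test hard to interpret, because the groups being compared are themselves shaped by treatment.

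At stake is how the mortality hazard ratios are read. The discussion presents the trial as groundwork for a larger study powered on survival and neurological outcome. A hazard ratio near or above 1 from a marker-conditioned model could be taken as evidence against a survival benefit when it shows no such thing.

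**Working it through.** **Step 1: timing.** This needs no arithmetic.

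| Variable | Relative to the infusion |
|---|---|
| Sex, age, primary ECG rhythm, time to ROSC | Before |
| NSE, IL-6 | After: first sample at hospital admission |
| pPCI performed | After: the infusion is pre-hospital |

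The admission sample is not a safe substitute for a baseline value. The background section attributes to glucocorticoids a non-genomic action that begins within seconds to minutes. The article does not say which sampling time feeds the Cox models. Any later time also requires the patient to survive until sampling, and the sample size section expects about 20% to die within 72 h.

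**Step 2: is there a figure to reproduce?** No. The article gives no number for the Cox analysis. The sample size section gives no SD either, but one can be back-solved on the log scale (an assumption), with SD = |ln 0.80| × √(N/4) / (z_α + z_β). For N = 114, power 0.90 and two-sided alpha 0.025, this is 0.223 × √28.5 / (2.241 + 1.282) = 0.34. One-sided, it is 0.37.

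**Step 3: size, by simulation.**

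- From the documents: the marker is lowered by 20% (log shift ln 0.80 = −0.223), and mortality is about 50% (the background gives 30-day mortality above 50%).
- Assumed: log-SD of the marker 0.4 to 1.0; log-hazard of death 0.5 or 1.0 per SD of marker; no effect of the drug on death except through the marker.
- Optional assumed severity factor: it explains half the marker's within-arm variance and adds 0.7 to the log-hazard per SD.
- Runs: 20,000 patients, three runs per scenario, 46% to 51% deaths.

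Mean hazard ratios for treatment:

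| Log-SD | Log-hazard per SD | Arm only | Arm + marker | Arm only, with severity | Arm + marker, with severity |
|---|---|---|---|---|---|
| 0.4 | 0.5 | 0.765 | 0.992 | 0.814 | 1.276 |
| 0.4 | 1.0 | 0.646 | 0.994 | 0.704 | 1.286 |
| 0.6 | 0.5 | 0.840 | 0.997 | 0.873 | 1.188 |
| 0.6 | 1.0 | 0.749 | 1.006 | 0.807 | 1.195 |
| 1.0 | 0.5 | 0.884 | 0.987 | 0.944 | 1.133 |
| 1.0 | 1.0 | 0.840 | 1.001 | 0.871 | 1.096 |

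Adding the arm-by-marker interaction, which is closer to what the article describes, and reading the treatment term at the mean marker value gives 0.99 to 1.00 without the severity factor and 1.10 to 1.29 with it.

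The simulated drug has no direct effect on death, so values above 1 in the last column are bias. They are not a true direct effect. The assumed SDs of 0.4 to 1.0 all exceed the back-solved 0.34 to 0.37, so the standardised drug effects used are smaller than the sample size implies on that reading.

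**Step 4: set against the trial's precision.** With 156 patients and 50% mortality there are 78 deaths, so SE(log HR) ≈ 2/√78 = 0.23. The shift caused by conditioning runs from ln(0.987/0.884) = 0.11 to ln(1.286/0.704) = 0.60, or about 0.5 to 2.7 standard errors.

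**The case against.** Much of the case on the other side stands.

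- **The mortality comparison is not wholly compromised.** A reader might infer that the trial's result on death will be biased. The article does not support that. The log-rank test and Kaplan-Meier plots are unadjusted and remain valid. However, they give no hazard ratio, and the Cox models are the only regression the article describes that would supply one.
- **Sequential adjustment may mean one variable at a time.** If so, the models for sex, age, rhythm and time to ROSC are sound. A reader might count treatment, seven main effects and seven interactions as 15 terms against about 78 deaths, or roughly 5 deaths per term. That presumes one joint model, which the text does not state, so it is not part of this point.
- **pPCI is a weaker case.** It follows the drug, but nothing in the article suggests that the drug changes who receives it, and no pPCI bias was simulated.
- **The sizes rest on assumptions.** Where the true hazard ratio is near 0.9 there is little to erase. At trial size, a point estimate of 1.29 has a 95% interval of exp(0.255 ± 1.96 × 0.226), about 0.83 to 2.01. It would not by itself establish harm.
- **Mortality is secondary.** The trial is phase II, powered on biomarkers, and its discussion calls the results hypothesis-generating.

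The argument that an SAP may settle the matter helps less. The sampling time and the handling of deaths before sampling could reasonably be left to it. The choice of variables is not left open: the article names them, and does not label the models exploratory or as mediation analyses.

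**Conclusion.** The point holds for the Cox models that include NSE or IL-6, which are wrong as written if read as treatment effects on death. Conditioning on a co-primary endpoint measured after the drug does not give the total effect, and interactions with it are not valid subgroup tests. This follows from the timing alone.

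The direction and size of the error depend on the drug lowering the markers (the trial's hypothesis), on the markers predicting death (the background section says this of both), and on the assumed SDs and slopes. Within those assumptions a fully mediated benefit of 0.65 to 0.88 is estimated at about 1.0. With shared unmeasured severity, 0.70 to 0.94 is estimated at 1.10 to 1.29.

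The stronger reading, that the plan would turn a survival benefit into a null or harmful mortality result overall, is not supported, given the intact log-rank comparison and the limited precision. The primary biomarker analysis and the sample size are untouched. Severity is moderate.

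**What to change.** Replace the Cox sentence with wording to this effect:

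- Report one treatment hazard ratio for mortality, adjusted only for the main effects of age, sex, primary ECG rhythm and time to ROSC, alongside the log-rank test.
- Limit treatment interaction tests to these four pre-randomization variables, one at a time, labelled exploratory.
- Remove NSE, IL-6 and pPCI from the Cox treatment-effect models.
- Put any interest in NSE or IL-6 as pathways in a separate, labelled exploratory mediation or landmark analysis that states the sampling time and how deaths before sampling are handled.

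The cost is a few lines of analysis wording, with no extra patients, samples or data. The change should be made before allocation is unblinded. Since the amendments section {25} says that the current protocol will not be changed further, the SAP is the natural place for it.

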#### Interim analyses {21b}

For monitoring of general safety, interim analyses of mortality and hospital length of stay will be performed after 60 participants have been included in the trial.

#### Methods for additional analyses (e.g., subgroup analyses) {20b}

Additional subgroup analyses will be performed on patients with ST-elevation myocardial infarction (primarily suspected in the ECG followed by pPCI) to decide whether active study drug, methylprednisolone, can mitigate the cardiac injury.

Another subgroup will be patients not intubated at admission since a part of included patients will wake up sufficiently, so intubation is not needed and therefore not go to the ICU. Primarily, the changes in markers of inflammation will be compared according to allocation to study drug or placebo and secondarily awake patients will be compared with comatose patients.

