#### Intervention description {11a}

Patients allocated to methylprednisolone will receive a bolus infusion of 250 mg over 5 min. The study drug is prepared by a simple shaking-mechanism where 2 × 125 mg/2 mL of methylprednisolone powder is mixed preservative-free to a total volume of 4 mL. Patients allocated to placebo will receive a 4 mL infusion of isotonic saline. Infusion of study drug or placebo will be made as soon as possible following 5 min of stable ROSC in the pre-hospital setting.

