Several studies have demonstrated the molecular mechanisms of glucocorticoids, and it is clear that the effects work both through genomic and non-genomic pathways [23, 35], whereas genomic effects alter protein expression within hours, non-genomic effects are believed to kick in within seconds to minutes. A recent review reported rapid non-genomic anti-inflammatory properties both in transformed and immune cells and concluded that these effects are not well understood but could have significant therapeutic value [36]. Further, both genomic and non-genomic effects of glucocorticoids on the cardiovascular system have been suggested to induce an increase in both blood pressure and contractility [37, 38]. Similarly, evidence indicates that glucocorticoids may effectively treat neuroinflammation, which may be comparable to the condition seen in PCAS. Still, the mechanisms are both poorly understood and investigated [39, 40]. As the intervention in this study is a high dose of methylprednisolone injected shortly after ROSC, we hope to achieve essential knowledge about the beneficial non-genomic effects of glucocorticoids by mitigation of the inflammatory part of PCAS at the earliest stage possible and hereby possible improving hemodynamic parameters and neurological stunning. The results of this study should be interpreted as hypothesis-generating in terms of the need to conduct a larger scale study powered towards clinical endpoints such as survival and neurological outcome.

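### Comparing the arms among patients not intubated on admission conditions on waking after the infusion, so randomization does not protect that contrast

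*Protocol article*

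**What the plan says.** The section on additional analyses {20b} of the protocol article names two subgroups.

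- **Non-intubated patients.** "Another subgroup will be patients not intubated at admission since a part of included patients will wake up sufficiently". The primary comparison inside this group is between arms: "the changes in markers of inflammation will be compared according to allocation to study drug or placebo". Awake against comatose patients comes second.
- **STEMI patients**, identified as "primarily suspected in the ECG followed by pPCI". The stated purpose is "to decide whether active study drug, methylprednisolone, can mitigate the cardiac injury".

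Other sections fix the timing. The inclusion criteria require GCS ≤ 8 at randomization. Section {11a} states: "Infusion of study drug or placebo will be made as soon as possible following 5 min of stable ROSC in the pre-hospital setting". Section {17a} adds: "Infusion is completed before arrival at the hospital". The Discussion says that "non-genomic effects are believed to kick in within seconds to minutes" and hopes for "hereby possible improving hemodynamic parameters and neurological stunning". Section {20b} attaches no caution to either subgroup.

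**The concern.** A subgroup comparison inherits the protection of randomization when membership is fixed before treatment or cannot be affected by it. Membership here turns on waking after the drug has been given. If methylprednisolone brings some patients round who would have stayed comatose on placebo, the awake group in the active arm takes in patients who were sicker to begin with. Their inflammation markers would then tend to be higher for reasons unrelated to any anti-inflammatory action, and the contrast would understate a benefit. A reader of the results would have no way to tell this from a weak drug effect in awake patients.

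There is a second possible route. By section {17a}, the pre-hospital physician and assistant know the allocation once the box is opened, so an airway decision taken between then and arrival could depend on allocation. The direction of any bias by that route is unknown.

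**Working it through.** The plan gives no figure for this point, so there is nothing to reproduce. The check has three parts.

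**1. Order of events.** GCS ≤ 8 at randomization (inclusion criteria), then infusion (section {11a}), then arrival with the infusion complete (section {17a}), then airway status on admission (section {20b}). Membership is observed after treatment. The Discussion puts non-genomic effects at seconds to minutes and hopes for less neurological stunning, so on the protocol's own hypothesis the drug could act on waking before arrival.

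**2. Size of the bias when the drug has no effect on the marker.** The documents give no waking rates or severity–marker correlation. All inputs below are assumptions.

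*(a) Perfect selection: exactly the least severe fraction p wakes.* On a standard normal severity scale, mean severity in the awake group is −φ(z_p)/p.

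- p = 0.15: −1.554
- p = 0.25: −1.271
- Difference: 1.554 − 1.271 = 0.283 SD of severity

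Marker bias is this difference times the severity–marker correlation ρ.

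| Waking, placebo vs active | Severity SD | Marker SD, ρ = 0.3 | Marker SD, ρ = 0.7 |
|---|---|---|---|
| 10% vs 15% | 0.201 | 0.06 | 0.14 |
| 15% vs 25% | 0.283 | 0.08 | 0.20 |
| 10% vs 20% | 0.355 | 0.11 | 0.25 |

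*(b) Imperfect selection, by simulation.* Each scenario had 2,000,000 patients allocated 1:1. Severity U is standard normal. The log marker is 0.8 × (ρU + √(1 − ρ²)e), with e standard normal and no drug term. The log-odds of waking are logit(b) − U + ln(OR) for active patients and logit(b) − U for placebo, with b = 0.1, 0.2 or 0.3 and ρ = 0.3, 0.5 or 0.7. The last column is the active-to-placebo marker ratio among awake patients; the true value is 1.

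| Waking OR | Awake, placebo | Awake, active | Spurious ratio |
|---|---|---|---|
| 1 | 13–33% | 13–33% | 1.00 |
| 1.5 | 13–33% | 18–41% | 1.01–1.04 |
| 2 | 13–33% | 22–47% | 1.03–1.07 |
| 3 | 13–33% | 29–55% | 1.04–1.11 |

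The log ratio scales with the assumed marker SD of 0.8. If the sample size in section {14} is read on the log scale with a two-sided alpha of 0.025 and 112 patients, the implied SD is 0.223 × √(112/4) / (2.241 + 1.282) = 0.335, where 0.223 = −ln 0.80. At OR 2 the ratios then shrink to exp(ln 1.025 × 0.335/0.8) = 1.01 and exp(ln 1.068 × 0.335/0.8) = 1.03.

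*Against the planned effect.* A 20% reduction is a ratio of 0.80. Multiplied by the largest simulated bias, 0.80 × 1.11 = 0.89. At OR 2 with the larger bias, 0.80 × 1.07 = 0.86.

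**3. The STEMI subgroup.** The infarction precedes the drug, but the definition also asks that pPCI followed, and pPCI comes after the infusion. Membership therefore needs survival to the procedure and selection for it. Table 1 lists an ECG at 0 h without saying whether it precedes the infusion. The calculations above concern waking only and say nothing about the size of any bias here.

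**The case against.** The strongest reply is that measuring a subgroup variable after treatment causes bias only if treatment changes membership. That is correct, and the OR 1 row shows it. A single bolus shortly before arrival may wake nobody extra. Some patients may also have been intubated before the drug was given, which would limit its influence, although the stated definition does not separate them. But the plan cannot rest on the drug having no effect on waking while hoping that it improves neurological stunning.

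It can also be said that section {20b} compares changes, which may remove part of an imbalance in level. This has some force. However, the first sample is taken at admission, after the infusion, so there is no pre-drug value to correct against.

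These are additional analyses in a phase II trial whose results the Discussion calls hypothesis-generating. That limits the consequence but does not tell readers that this contrast is non-randomized.

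Three stronger readings are tempting, and the documents do not support them:

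- **That the bias would reverse a real effect.** At the planned 20% reduction, even the largest simulated bias leaves 0.89, which is attenuation.
- **That the 0.28 SD gap can be set directly against the effect the trial is powered for.** It is on the severity scale under perfect selection and must first be multiplied by the severity–marker correlation.
- **That the STEMI comparison is compromised to the same degree.** The infarction precedes the drug and in-hospital staff are blinded. The protocol suggests no route from the bolus to selection for pPCI beyond survival to the procedure.

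**Conclusion.** The point holds for the non-intubated subgroup. Its arm comparison conditions on a post-treatment response that the protocol's own hypothesis says the drug could affect, and nothing else in the article corrects for this. The likely direction is attenuation of a benefit, provided that the drug increases waking, sicker patients wake less often and sicker patients have higher markers.

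The size is zero if waking is unaffected and modest otherwise: about 0.08 to 0.20 SD of the marker for 15% versus 25% waking under perfect selection, or ratios of about 1.03 to 1.07 at a waking odds ratio of 2 under imperfect selection with a log-marker SD of 0.8. Every one of these inputs is an assumption.

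For STEMI the point is secondary and weaker: a definition that depends on a later procedure is best avoided. The co-primary analysis and the sample size do not depend on either subgroup.

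**What to change.** - **Non-intubated patients.** Report non-intubation on admission by arm as an outcome in all randomized patients. Present inflammation markers in awake patients in a descriptive table, labelled as a non-randomized comparison, with no treatment effect claimed.
- **STEMI.** Drop the requirement that pPCI followed. Define the subgroup by an ECG recorded before the study box is opened, if one exists. If none does, label the comparison exploratory and say why.

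The cost is analysis wording, plus a check on when the 0 h ECG was taken relative to the infusion. The trial gives up a formal arm contrast among awake patients, and a STEMI group defined by ECG alone may be slightly less specific.
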